### Setting

Five Pennsylvania NHs that vary in size, ownership, reimbursement patterns, and location will be used in order to provide a large population for recruitment, afford diversity, and enhance the generalizability of the findings for future translational research. The NHs range in size from 159 beds to 404 beds, with a total number of 1,355 beds. All but one have a segregated dementia unit, ranging in size from 30 beds to 60 beds, for a total of 143 beds. Based on previous pilot data[35] and information provided by the NH administration, approximately 20% of the sample of 1,355 potential subjects meets the inclusion criteria, resulting in a recruitment pool of 270 NH residents from which the final sample of 60 NH subjects will be obtained.

### Recruitment, Sample, Sample Size

Power analyses were conducted in order to determine the sample size needed to provide sufficient power (1-β > .80) for assessing relationships between the explanatory variables and resistive behaviors and oral health outcomes. Data from the pilot study informed these analyses[35]. The power analyses were conducted using the software PINT[46], which is based on the work of Snijders and Bosker[47,48]. PINT estimates standard errors for regression coefficients in a two-level model, from which power can be calculated for a given effect size and significance level (α). Effect size was taken to be the absolute value of a standardized regression coefficient, and α was set at 0.05. Because PINT is designed for a two-level model rather than a three-level model, the second and third levels (participant and nursing home) were combined for power analysis purposes. Inputs into PINT include the total number participants to be sampled across all nursing homes (*N*) and the number of data collection times (*n*) per participant. Given *N *and *n*, the total sample size is *N *× *n*. Plausible effect sizes and other required inputs into PINT were based on the pilot study[35].

Based on results from the pilot study,[35] it is plausible to expect that the intervention group-control group dummy variable will have an effect size of 0.05 or larger in both the models for care resistive behaviors and the models for oral health outcomes. Power will then be high (1-β > 0.90) provided there are 42 observations per participant (twice daily for 21 days, so that *n *= 42), 12 participants across both the intervention and control groups within each nursing home (assuming 16 participants recruited, less 25% attrition), and five nursing homes (so that *N *= 12 × 5 = 60). This corresponds to a sample size of 2,520 (*N *× *n *= 42 × 60 = 2,520). If the effect size is somewhat larger (0.1), power is extremely high (1-β ≈ 1). In summary, given a 25% expected attrition rate, 80 participants should be recruited for the study (40 in intervention and 40 in control groups).

Subjects will be recruited according to the following **inclusion criteria: **English-speaking; age 65 or older; documented diagnosis of dementia, Alzheimer's disease, vascular dementia, or Lewy body dementia; identified by NH staff as resistant to mouth care; at least 2 adjacent teeth AND/OR daily wearing of at least one denture plate; the ability to hold a toothbrush; and the ability to move his or her hand to his or her mouth. Once subjects are identified, consent will be obtained initially from the responsible party. After consent is obtained, subjects will be tested using the Mini-mental Status Examination (MMSE)[49]. Those with scores 18 or higher will be evaluated for the capacity to sign a consent form using a modification of Resnick et al.'s Evaluation to Sign Consent instrument[50]. This evaluation includes 8 questions that assess understanding of the study. Participants with dementia must score at least 6 out of the 8 questions correctly in order to sign the consent form. If the elder is deemed unable to sign the consent form assent will be obtained during each interaction between the NH resident and any member of the research team. **Exclusion criteria **are: age less than 65; no documented diagnosis of dementia; inability to hold a toothbrush; inability to raise his or her hand to his or her mouth; receiving treatment for an active dental or denture problem; or a diagnosis of dysphagia requiring thickened liquids.

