## Methods/Design

A randomized repeated measures design will be used in this clinical trial. NH residents will be randomized at the individual level to the experimental group, which will receive the intervention, or to the control group, which will receive standard mouth care from research team members who receive training in the proper methods for providing mouth care but no training in resistance recognition or resistance prevention/mediation. For baseline data collection, the behavior raters (research assistants trained to observe and record CRB) will observe both control and experimental NH residents receiving mouth care from the NH staff twice daily (AM: after breakfast but before lunch and PM: immediately after the evening meal) for 7 days. Members of the experimental and control groups will then receive mouth care from interventionists (research team members trained to provide mouth care) twice daily for 21 days, using the same schedule. A 21-day intervention period provides the greatest opportunity for obtaining the maximum benefit from the MOUTh intervention. Oral health outcome data will be collected 5 times: once prior to the 7-day observation period; once after the 7-day observation period but before the initiation of the intervention; after 7 days of intervention; after 14 days of intervention; and after 21 days of intervention. This schedule, which is depicted in Table 1 is designed to fully capture changes in oral health throughout the progression of the study.

**Table 1 T1:** Intervention & Data Collection Schedule

	Steps & Measures	Frequency
Recruitment	**Screen and Consent** Written consent from responsible party Examination of medical records to confirm inclusion/exclusion criteria Examination of NH resident for ability to hold toothbrush, raise hand to mouth MMSE Resnick et al.'s Evaluation to Sign Consent if MMSE 18 or higher Written consent from NH resident if 6/8 questions answered correctly on Resnick et al.'s Evaluation to Sign Consent	Once

Baseline, pre-observation	**Randomization (Experimental or Control) and Baseline** Baseline Chart Review (demographic data, co-morbidities) Global Deterioration Scale (GDS) Katz Activities of Daily Living (ADL) Oral Health Assessment Tool (OHAT)	Once Once Once

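### The power stated for the oral health models assumes 42 observations per resident, but the OHAT is scored only 5 times, 3 of them during the intervention

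*Protocol article*

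**What the plan says.** The section Recruitment, Sample, Sample Size of the protocol article gives one power analysis and says that it serves both resistive behaviours and oral health outcomes. It defines n as "the number of data collection times" per participant. On scale and level it says "Effect size was taken to be the absolute value of a standardized regression coefficient" and "α was set at 0.05". It then expects, from the pilot study, an effect of at least 0.05 "in both the models for care resistive behaviors and the models for oral health outcomes". The next sentence opens "Power will then be high (1-β > 0.90" and makes this conditional on n = 42 (two sessions a day for 21 days) and N = 60 (12 residents in each of five homes after 25% attrition), a total of 2,520. It adds: "If the effect size is somewhat larger (0.1), power is extremely high". No separate n or power is given for oral health.

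The opening of Methods/Design says: "Oral health outcome data will be collected 5 times: once prior to the 7-day observation period". The other four scores follow the observation week and each of the three intervention weeks. Table 1 agrees: in the intervention phase, mouth care and the RTC-r are twice daily for 21 days, while the OHAT is taken after Days 14, 21 and 28. Under Instruments and Measures, the total OHAT score is the outcome for Aim 2 and H2, and the Background lists Aim 2 among the primary specific aims.

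**The concern.** The condition on which the power figure depends cannot be met for the OHAT. The plan's 42 counts intervention sessions only, since the 7 baseline days would add 14 more. The like-for-like OHAT count is therefore 3, or 5 if both baseline scores enter the model. This is not a detail left to a fuller document. The article states a power figure for oral health and ties it to a measurement count that its own schedule rules out. At stake is whether a primary aim has a usable power statement.

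**Working it through.** **Inputs from the article:** N = 60; n = 42 as stated; OHAT count 5 in all, 3 on intervention; α = 0.05; standardised coefficient b = 0.05 (also 0.1); equal allocation.

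**Assumptions, because the article does not give them:** two-sided test; intraclass correlation (ICC) of 0 to 0.7; residual variance share 1 − R².

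**Counts.** 60 × 42 = 2,520 and 60/(1 − 0.25) = 80 both reproduce. For the OHAT, 60 × 5 = 300 and 60 × 3 = 180.

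**Formula** (normal approximation, group as a participant-level variable):
SE = √[(1 − R²)(ICC + (1 − ICC)/n)/N]; power = Φ(b/SE − 1.960).

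**Step 1: the plan's own figure.** With n = 42, ICC = 0 and R² = 0, SE = √(1/2,520) = 0.0199, b/SE = 2.51 and power = 0.71 (0.81 one-sided). At b = 0.1 power is 0.999. The stated value above 0.90 at b = 0.05 therefore needs inputs that are not shown, for example a residual variance share of 0.60 or less at ICC = 0.

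**Step 2: the scheduled OHAT counts, same assumptions.**
- n = 5: SE = √(1/300) = 0.0577, b/SE = 0.866, power 0.14 (0.41 at b = 0.1).
- n = 3: SE = √(1/180) = 0.0745, b/SE = 0.671, power 0.10 (0.27 at b = 0.1).

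**Step 3: give the plan its 0.90.** Choose 1 − R² so that n = 42 yields exactly 0.90 at b = 0.05:
1 − R² = (0.05/3.2415)² × 60/(ICC + (1 − ICC)/42), where 3.2415 = 1.960 + 1.2816. Then change only n.

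| ICC | 1 − R² needed | n = 42 | n = 5 | n = 3 |
|---|---|---|---|---|
| 0 | 0.600 | 0.900 | 0.200 | 0.137 |
| 0.1 | 0.118 | 0.900 | 0.569 | 0.431 |
| 0.3 | 0.045 | 0.900 | 0.785 | 0.705 |
| 0.5 | 0.028 | 0.900 | 0.849 | 0.811 |
| 0.7 | 0.020 | 0.900 | 0.878 | 0.862 |

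At b = 0.1 the same calibration gives 0.609 (n = 5) and 0.410 (n = 3) at ICC 0, 0.990 and 0.947 at ICC 0.1, and about 1 from ICC 0.3 upward.

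**Step 4: how much of the problem is n.** The coefficient detectable with 90% power (R² = 0) is 3.2415 × √[(ICC + (1 − ICC)/n)/60].

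| ICC | n = 42 | n = 3 |
|---|---|---|
| 0 | 0.065 | 0.242 |
| 0.3 | 0.235 | 0.306 |
| 0.5 | 0.299 | 0.342 |
| 0.7 | 0.352 | 0.374 |

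The measurement count dominates when the ICC is near 0 and matters little when it is high.

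**The case against.** The strongest reply is that group is a participant-level variable, so when scores within a resident are highly correlated, extra measurements add little and losing them costs little. OHAT scores taken weekly in the same mouth may well be highly correlated. The PINT inputs came from the pilot and are not shown, many covariates enter the model, and 0.05 is a floor for the effect. In Step 3, three scores still give 0.81 at ICC 0.5 and 0.86 at ICC 0.7, above the general 0.80 target in the same section. That no entry there reaches 0.90 follows from calibrating to exactly 0.90. If the PINT run gave clearly more at n = 42, the OHAT figure could be higher too.

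Much of this stands, and it rules out two stronger readings. A reader might infer that the trial can detect only OHAT effects 6 to 7 times the planned 0.05. Step 4 shows that, at ICC 0.3 to 0.7, most of that multiple would remain with 42 OHAT scores: it comes from N = 60 and the assumed ICC. A reader might also take the 10% power at independence as an upper bound. It is not, because it allows no variance explained by covariates.

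The reply does not rescue the stated figure. The high-ICC cases require covariates to explain about 95% to 98% of the variance. The article's own OHAT reliability figures (0.78 intra-carer, 0.74 inter-carer) make that hard to accept. If they are read, as an assumption, to leave 22% to 26% of variance as measurement error, and covariates explain all the rest, then SE = √(0.22/180) = 0.035 to √(0.26/180) = 0.038, and power with three scores is 0.30 to 0.26. With five scores it is 0.45 to 0.40.

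**Conclusion.** The concern holds as an inconsistency between the power inputs and the measurement schedule. The multiplication giving 2,520 is correct, but it does not describe the oral health data. The stated power for Aim 2 is unsupported, both above 0.90 at 0.05 and near 1 at 0.1.

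The size of the shortfall depends on unpublished inputs. At an effect of 0.05 with N = 60 and a two-sided test, power is 0.14 (5 scores) or 0.10 (3 scores) under independence with no covariate gain. When n = 42 is calibrated to 0.90, it lies between 0.20 and 0.88 (5 scores) or 0.14 and 0.86 (3 scores).

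A reader might go further and conclude that Aim 2 is certainly underpowered, or that a null H2 result will be misread. The article supports neither: a larger OHAT effect, or a more favourable PINT result than 0.90, could leave power adequate. It simply does not show this.

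**What to change.** Limit the sentence with 42 observations per participant and the total of 2,520 to the care-resistant behaviour models. Keep the pilot-based effect-size expectation for oral health, since that sentence is not where the fault lies. Rerun PINT for the OHAT with N = 60 and the scheduled number of scores: n = 5 if both baseline scores are modelled with the planned baseline-versus-intervention dummy, or n = 3 if only intervention-phase scores count. Restate Aim 2 power, or the detectable OHAT difference, together with the ICC and residual variance used.

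The cost is one further PINT run and a few lines of text. The design, the schedule and the target of 80 need not change for this correction. The downside is that the Aim 2 figure will be less favourable than the one now printed.

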This protocol is innovative in specifically addressing threat perception and fear responses in individuals with dementia who are unlikely to have sufficient contextual or cognitive control over threat perceptions due to altered neurological structures and functions. The specific strategies proposed here are expected to reduce perceptions of mouth care and caregiver as threatening and, in turn, limit or prevent CRBs associated with automatic and reflexive fear responses.

In summary, there is a tremendous gap in knowledge regarding interventions designed to prevent and reduce CRB during mouth care in order to improve the oral health of persons with dementia. Persons with dementia and CRB have been systematically excluded from intervention studies developed to improve oral health among NH residents, even though older adults with moderate to severe dementia have worse oral health those with no or mild dementia. Interventions to address oral health outcomes for NH residents with moderate to severe dementia, and who resist care, have not been systematically examined in either nursing or dental research studies. In order to improve nursing clinical practice and to address oral health disparities, it is imperative to design studies that focus on these interventions.

The purpose of this study is to determine whether CRBs can be reduced, and oral health improved, through the application of an intervention based on the neurobiological principles of threat perception and fear response. **The primary specific aims of the study are to:**

1. Evaluate the efficacy of the Managing Oral Hygiene Using Threat Reduction (MOUTh) intervention for reducing CRBs in persons with dementia;

2. Validate the overall efficacy of the MOUTh intervention using nurse-sensitive oral health outcomes-- swollen and bleeding gums, cleanliness of the oral cavity, saliva, and integrity of the lips and oral mucosa; and

3. Calculate the cost of the MOUTh intervention.

The hypotheses based on the specific aims are as follows:

H1. Implementation of the MOUTh intervention will significantly reduce CRBs during mouth care compared to usual mouth care;

H2. The MOUTh intervention will improve oral health in older adults with dementia through the resolution of swollen and bleeding gums, improved cleanliness of the oral cavity, and the resolution of dry, cracked, and fissured oral mucosa and lips compared to usual care.

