### Description of Usual Care

Usual mouth care is a challenging issue. For many persons who resist care, "usual" mouth care may mean NO mouth care[27]. Designing a study in which a potentially powerful intervention is compared to an absence of care would be meaningless. In order to have parity between the control and experimental groups, members of both will receive mouth care from interventionists from the research team. The difference will be that the control interventionists will NOT receive training in techniques designed to prevent and reduce CRB. Instead, the control interventionists will receive training separate from the experimental interventionists. That training will consist of best mouth care practices specific to older adults[36-40]. For consistency, both subjects in the control and experimental groups will receive the same mouth care supplies during the duration of the study: Biotene™ toothpaste (dentate); Biotene™ alcohol-free mouthwash (both); soft toothbrushes (dentate); denture brushes (dentures); interdentate sticks (dentate); denture cleansing paste (denture); and denture cups.

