### Randomization and Control of Cross-Contamination

Randomization will be concealed until after the initial screen and consents are obtained and an ID number is assigned to the subject. [name] will prepare sealed envelopes to implement randomization. Inside each envelope will be the subject's group assignment, determined using a random number generator, with randomization to be conducted in blocks by nursing home site and time to ensure equal assignments across the two groups at the completion of the study and approximately equal assignments throughout the study to control for unknown temporal effects. While randomization by site is an acceptable method for controlling cross-contamination of conditions, we will randomize by individual. The rationales for this decision are, first, nursing homes are unstable environments[51] and second, nursing home quality indicators can fluctuate from one six-month period to the next[52]. Changes in quality indicators may reflect changes in resident profiles and/or changes in quality of care, both of which could affect the results of our study if randomization occurred at the facility level. Randomization by subject will provide greater power than randomization by NH.

Cross-contamination is a significant threat because control and experimental interventionists have the potential to interact during the provision of mouth care. Training for CRB raters, control interventionists, and experimental interventionists will occur separately. There will be no cross-training. All team members will be blinded to the specific aims of the study. All team members (CRB raters, interventionists) will be blinded to their assignment to the control or experimental arms of the study. Interventionists will be instructed to provide mouth care in private bathrooms with only the CRB rater present, to avoid having interventionists inadvertently observe each other. CRB raters will be paired exclusively with their control interventionists or with their experimental interventionists, to avoid bias in rating.

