### Statistical Analysis

Individual growth models using multilevel analysis will be used to estimate the efficacy of the intervention for reducing CRBs in persons with dementia, and to estimate the overall efficacy of the intervention using oral health outcomes. Multilevel models (also referred to as hierarchical linear models) will be used because repeated observations of participants are nested within nursing homes[48,64-68]. Multilevel models deal with the "unit of analysis" problem that face nested studies, that is the units of analysis are not independent, but instead the observations are clustered[48,66,69,70]. Because multiple observations are nested

within participants (i.e., repeated measures), individual growth models will be used. Among the advantages of using individual growth models are the ability to deal with an unequal number of measurement occasions among individuals and heterogeneity of variance[48,65,66,71].

Three-level multilevel models will be estimated for CRBs and oral health outcomes in which the first level is the date/time at which the behaviors or outcomes are observed; the second level is the participant; and the third level is the NH in which the participant resides. Explanatory variables to be included at the first level are dosage; frequency; time; and a dummy variable for baseline versus intervention. Explanatory variables to be included at the second level are a dummy variable for whether the participant is in the intervention group or control group; functional status; cognitive impairment; demographic data (gender, ethnicity, race, age, duration of stay in a nursing home); co-morbid conditions; and the use of psychoactive medications. Variables are discussed and defined above.

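### Type of dentition is known before randomisation and shapes the mouth care given, but is not among the model's listed covariates; adding it is a minor, nearly free gain in precision

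*Protocol article*

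**What the plan says.** The inclusion criteria (Recruitment, Sample, Sample Size) accept residents with "at least 2 adjacent teeth AND/OR daily wearing of at least one denture plate". Three kinds of resident can therefore enter: natural teeth only, dentures only, or both.

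Description of Usual Care gives both arms the same products, but most are issued by dentition: "soft toothbrushes (dentate); denture brushes (dentures); interdentate sticks (dentate); denture cleansing paste (denture); and denture cups".

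Randomization and Control of Cross-Contamination provides for "randomization to be conducted in blocks by nursing home site and time". Dentition is not a factor.

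Statistical Analysis names the model terms. At the observation level: "Explanatory variables to be included at the first level are dosage; frequency; time; and a dummy variable for baseline versus intervention". At the resident level: the arm dummy, then "functional status; cognitive impairment; demographic data (gender, ethnicity, race, age, duration of stay in a nursing home); co-morbid conditions", and psychoactive medication. Dentition appears at neither level. No arm-by-phase interaction and no baseline value of the outcome is named. The power calculation likewise attaches its effect size to the arm dummy, with the 42 intervention-phase observations per resident.

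**The concern.** Dentition is fixed before randomisation and could plausibly predict both outcomes. The second hypothesis works partly "through the resolution of swollen and bleeding gums, improved cleanliness of the oral cavity". Each category of the Oral Health Assessment Tool (OHAT) relates to particular structures of the mouth. The care task itself also depends on whether there are teeth to brush or a denture to clean.

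The covariate list is explicit and goes down to ethnicity and length of stay, yet it leaves out a characteristic that the trial already needs for eligibility and supplies. In a contrast between residents, variance due to dentition stays in the error of the arm coefficient, and a chance difference between arms in the share of denture wearers is not adjusted for. What is at stake is precision, and how well the estimate from the one trial actually run reflects like-for-like residents.

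**Working it through.** **The plan's own figures.** 12 residents × 5 homes = 60 analysed; 60/(1 − 0.25) = 80 recruited, so 40 per arm, or 30 per arm after the stated attrition. These reproduce.

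**Assumptions, since the article gives no figures.** Denture-only share p = 0.30 (range 0.20 to 0.50). Outcome difference by dentition g = 0.3 to 0.8 SD, where the SD is that of a single measurement within a dentition group. Intraclass correlation (ICC) 0.6 for OHAT, and 0.3 or 0.5 for care-resistant behaviour (CRB).

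**Step 1: how large is chance imbalance?** The SD of the arm difference in share is √(2p(1 − p)/n).
- n = 40: √(2 × 0.3 × 0.7/40) = 0.102, so about ±20 percentage points covers 95% of randomisations.
- n = 30: √(2 × 0.3 × 0.7/30) = 0.118, about ±23 points.

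Exact hypergeometric probabilities, ignoring the site blocks, over p = 0.20 to 0.50:

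| Imbalance | 40 per arm | 30 per arm |
|---|---|---|
| 10 points or more | 0.40 to 0.50 | 0.33 to 0.44 |
| 20 points or more | 0.05 to 0.12 | 0.10 to 0.20 |

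An imbalance of 10 to 20 points shifts an unadjusted comparison by between 0.10 × 0.3 = 0.03 SD and 0.20 × 0.8 = 0.16 SD. The average absolute imbalance is smaller, about 0.8 × 0.102 = 0.08, which gives 0.02 to 0.06 SD.

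**Step 2: what does adjustment gain in the model as written?** The variance of a resident's mean over m intervention-phase measurements is v = ICC + (1 − ICC)/m. Dentition adds a = p(1 − p)g². Adjusting multiplies the standard error by √(v/(v + a)) × √(57/56); the last factor is the average price of one extra covariate with 60 residents. With p = 0.30, a = 0.21 × 0.09 = 0.0189 at g = 0.3 and 0.21 × 0.64 = 0.1344 at g = 0.8.

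| Outcome | v | Reduction, g = 0.3 | Reduction, g = 0.8 |
|---|---|---|---|
| OHAT, m = 3, ICC 0.6 | 0.733 | 0.4% | 7.3% |
| CRB, m = 42, ICC 0.5 | 0.512 | 0.9% | 10.2% |
| CRB, m = 42, ICC 0.3 | 0.317 | 2.0% | 15.5% |

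**Step 3: does it matter if baseline is used?** OHAT was simulated with 30 residents per arm, two baseline and three later values, ICC 0.6, 40% denture-only, a stable dentition effect of 0.8 SD and a treatment effect of 0.5 SD (2,000 runs):

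| Analysis | SD of estimate | Power |
|---|---|---|
| Post-baseline values only | 0.243 | 0.50 |
| Same, plus dentition | 0.222 | 0.60 |
| Baseline-adjusted | 0.139 | 0.94 |
| Same, plus dentition | 0.138 | 0.945 |

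With no treatment effect, and dentition effects of 0, 0.5 and 0.8 SD, the rejection rate was 0.046 to 0.052 in all four analyses and the mean estimate was essentially zero.

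**The case against.** The strongest reply is that the design already holds the remedy. Every resident has two OHAT assessments and up to 14 CRB observations before the intervention starts, and these enter growth models with a baseline-versus-intervention dummy. A stable dentition effect is present in each resident's own baseline, and Step 3 shows that adding dentition then gains almost nothing. This stands for any analysis that estimates the arm effect as change from baseline. The printed list does not fix such an analysis: arm and phase are separate terms and their interaction is not named. For CRB the protection may also be weaker than the OHAT simulation suggests. Baseline CRB is observed under nursing home staff, whose usual care for resistant residents may, by the article's own account, be no mouth care at all.

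A second reply is that CRB is already a rate per minute and that session length (dosage) is a covariate. This answers part of the point about differing tasks. But session length is measured after randomisation and may itself be affected by arm, so it does not stand in for a pre-randomisation characteristic.

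Third, the list already holds about ten resident-level terms for 60 analysed residents, and an analysis plan that is not shown may add dentition. Both are fair and keep the point minor.

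Two stronger readings are tempting, and the documents support neither. A reader might infer that the comparison is biased or that false positives rise. Individual randomisation prevents this, and the ordinary standard error already allows for chance imbalance. A reader might also infer that some OHAT categories cannot apply to residents without teeth, so that the total should be rescaled. The article does not show the categories, and the reliability it reports (0.78 and 0.74) is for the total score. Rescaling is not recommended.

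**Conclusion.** The omission is real but minor. Dentition is absent from an explicit covariate list although the trial already uses it for eligibility and supplies. In the between-resident arm contrast as written, including it would lower the standard error by about 0 to 7% for OHAT and 1 to 15% for CRB. These figures rest on the assumed 30% denture-only share, a 0.3 to 0.8 SD effect and the stated ICCs; the article gives none of them. The gain nearly vanishes if the arm effect is estimated as change from baseline and the dentition effect is stable.

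A reader might also set the possible shift of 0.03 to 0.16 SD beside the planned standardised coefficient of 0.05 (0.05/0.5 = 0.10 SD for a 1:1 dummy) and conclude that imbalance could produce the result. That does not follow. In the post-baseline analysis the SD of the estimate is itself 0.22 to 0.24, and it includes this source of variation.

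**What to change.** In Statistical Analysis, add dentition (natural teeth only, denture only, both), recorded at screening, to the resident-level covariates of both the CRB and OHAT models. This takes one sentence and one or two degrees of freedom. It should need no new examination, because eligibility and supplies already require the information.

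Stratifying the randomisation is not needed. With 16 residents recruited per home, three dentition types would average about five each (16/3) before blocking by time. The OHAT total should stay as defined.
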